## Abstract

**Aims:**

Adherence therapy is a candidate intervention to improve medication adherence and clinical outcomes in patients with type 2 diabetes. The feasibility of conducting a trial of adherence therapy in this population has not been established. The objective of this study is therefore to test the feasibility of conducting a randomized controlled trial of adherence therapy in a Middle Eastern context.

**Design:**

A single‐centre randomized controlled feasibility trial of adherence therapy in patients with type 2 diabetes.

**Methods:**

We will undertake an initial cultural adaptation of a telephone‐delivered form of adherence therapy in four patients in a Middle Eastern context. Our subsequent feasibility trial will aim to recruit 40 non‐adherent diabetic patients that will be randomly allocated to receive eight weekly 30‐min telephone adherence therapy sessions delivered by a diabetes educator versus treatment as usual. Key outcomes of interest include the number of patients invited to take part in the trial that consent to participate and then go on to complete treatment.

**Result:**

The findings of this study will determine the feasibility of undertaking a full randomized controlled trial of adherence therapy in patients with type 2 diabetes.

## INTRODUCTION

1

The prevalence of diabetes mellitus is on the increase worldwide, doubling since 1980 from 4.7% of the adult population to 8.5% in 2014. The number of people living with diabetes is expected to continue to increase, affecting an estimated 550 million by 2030 and 642 million by 2040 (Ogurtsova et al., 2017).

Type 2 diabetes accounts for 90% of all diabetes cases worldwide (Ogurtsova et al., 2017). It is a long‐term condition and is associated with substantial financial burden, reduced quality of life and serious health complications including diabetic retinopathy, renal failure and heart disease (National Health Priority Action Council (NHPAC), 2006). It was estimated that five million deaths were associated with diabetic complications in 2015 (Roglic & World Health Organization [WHO], 2016). Maintaining an optimal haemoglobin A1C (HbA1c)—defined as the average blood glucose (sugar) levels for the last two to three months (Ogurtsova et al., 2017)—is a challenge for many patients. One of the biggest factors having an impact on glycaemic control is poor medication adherence (Egede et al., 2014; Pladevall et al., 2004).

## BACKGROUND

2

A systematic review of 27 studies involving approximately 500,000 patients with type 2 diabetes reported that medication non‐adherence with oral medication alone or in combination with injectable insulin ranged from 6.9% to 61.5% (Krass et al., 2015). An earlier systematic review of 17 studies involving more than 900,000 patients with type 1 and 2 diabetes observed that non‐adherence to insulin therapy ranged from 14% to 57% (Davies et al., 2013). The considerable variation in non‐adherence rates reported in these reviews is likely due to methodological problems in measuring patient adherence to treatment.

Poor adherence to medication is an important and often overlooked barrier to optimizing health outcomes in patients with diabetes (Sokol et al., 2005) and is an important clinical issue for nurses working with this group of patients. For people with type 2 diabetes treatment, adherence is not limited to medication but also includes adopting and complying with lifestyle changes (e.g. eating a healthy diet, taking regular exercise and self‐blood glucose monitoring).

Polonsky (2016) reported that the most common modifiable factors affecting medication adherence in people with type 2 diabetes were perceived treatment efficacy, hypoglycaemia, treatment complexity and convenience, cost of treatment, medication beliefs and physician trust. Polonsky (2016) also concluded that no specific intervention has consistently been shown to be effective at improving adherence and recommended that a new approach to enhancing adherence be developed to target both treatment‐related burden and beliefs about treatment (Polonsky & Henry, 2016).

A number of different adherence interventions have been tested in patients with type 2 diabetes including patient education, consultation and simplifying treatment regimes. A Cochrane systematic review of adherence interventions in type 2 diabetes included 21 randomized controlled trials involving 4,135 patients. The authors reported that most of the studies were of methodologically poor quality and it was not possible to conclude which intervention characteristics constituted an effective medication adherence intervention (Vermeire et al., 2005).

The WHO has published guidelines regarding strategies to improve adherence to long‐term therapies that inform nursing practice. The guideline recommends supporting patients and encouraging them to participate in a treatment plan. A focus on barriers to adherence (e.g. forgetfulness), as well as addressing patients’ beliefs about their illness and treatment, is also recommended. WHO suggests that the optimum solution to non‐adherence is an individualized consultation to address patients’ belief about illness and treatment and to encourage them by actively involving patients in their treatment plan and ongoing management. As far as we can determine there have been no specific tests of this approach in patients with type 2 diabetes (Santé et al., 2003).

Many of the strategies identified by the WHO to address non‐adherence are encapsulated in adherence therapy originally described by (Gray et al., 2006). Adherence therapy is a patient‐centred approach that incorporates cognitive behavioural (e.g. problem‐solving, challenging beliefs) and motivational interviewing (exploring ambivalence) techniques to enhance medication adherence (Gray, 2011).

Adherence therapy has been tested in a number of disease areas, including mental disorders (Chien et al., 2015; Gray et al., 2006; Schulz et al., 2013), hypertension (Alhalaiqa et al., 2012) and Parkinson's disease (Daley et al., 2014). For example, a randomized controlled trial of seven adherence therapy sessions facilitated by nurses versus treatment as usual was conducted with 136 non‐adherent patients with hypertension, resulting in significant improvements in adherence to treatment in the intervention group compared with the control group (Alhalaiqa et al., 2012). Similarly, Daley et.al (2014) tested adherence therapy facilitated by nurse specialists in a randomized controlled trial of 76 non‐adherent patients with Parkinson's disease. Improvements in both medication adherence and quality of life were reported by the patients who received adherence therapy (Daley et al., 2014). A systematic review and meta‐analysis of six randomized controlled trials involving 725 patients also showed that adherence therapy was effective at improving psychiatric symptoms in patients with severe mental illness with a medium effect size (SMD = 0.56). However, adherence behaviours and treatment attitudes did not improve significantly (SMDs of 0.25 and 0.43, respectively) (Gray et al., 2016). Importantly, research outcomes indicate that adherence therapy could potentially be facilitated by nurses as part of their routine clinical practice (Gray et al., 2004).

Whilst there may be merit to undertaking a trial of adherence therapy in patients with type 2 diabetes, consideration needs to be given as to how adherence therapy can be delivered as part of routine nursing practice as patients visit secondary care diabetes clinics infrequently (e.g. six monthly). Mobile telephone usage has become pervasive since the early 2000s and is a potentially novel way to deliver psychological interventions. Telephone‐delivered interventions may be preferred by patients because the interventions consume less time (e.g. there is no travel to and from a hospital) and can be more easily delivered at a time that fits in with their lifestyle (e.g. outside of normal clinic hours). Moreover, systematic reviews and meta‐analyses have reported that it is feasible to deliver psychological interventions over the phone (Fjeldsoe et al., 2009; Krishna & Boren, 2008; Liang et al., 2011).

The feasibility of conducting a trial adherence therapy trial in a Middle Eastern context is the research question that this study will address. A feasibility trial is a study undertaken to inform a main clinical trial. Important parameters that will inform main trial design can be tested. Typically, these include participants willingness to be randomized, subjects motivation to consent to take part in a trial and an estimated of the number of patients the meet eligibility criteria (Arain et al., 2010). In nursing science, this stage in the research process is often omitted substantially increasing the risk that a full trial will not recruit to time and target (Gray et al., 2019).

## THE STUDY

3

### Design

3.1

The study is in two parts: 1. a qualitative cultural adaptation, 2. a parallel group, unblinded, randomized controlled feasibility trial.

## METHODS

4

### Part one: Cultural adaptation

4.1

Adherence therapy has not been previously implemented in diabetes patients in a Middle Eastern context. To establish the acceptability of the therapy in the Middle East and to identify any required modifications to the intervention, a cultural adaption study will be completed prior to undertaking the feasibility trial. The study will explore patients’ willingness to actively participate in a therapy process that is focused on them reflecting on how best to manage their diabetes when the typical cultural expectation is for health professionals to be wholly responsible for managing the patient's illness (Chamsi‐Pasha & Albar, 2016). Most Middle Eastern countries have a strong Islamic tradition that likely has an impact on health beliefs. A review of 34 studies investigating determinants of patients’ behaviour in Middle Eastern countries showed that culture including lifestyle, self‐beliefs, religions and healthcare providers trust effect the management of type 2 diabetes. In Muslim society, religion plays an important role in how clinical care is delivered. For example, death and sickness are in God's plan and we have no control on it (Alsairafi et al., 2016). This may lead to a sense of passivity, whereby the individual does not think they have control or influence over their illness.

### Approach to cultural adaptation

4.3

#### Population

4.3.1

Four adults with type 2 diabetes from the National Guard Hospital in Riyadh, Saudi Arabia will be recruited. Patients will be approached by a member of the treating team and asked if they are interested in participating in the cultural adaptation study. If they agree, they will be asked for their contact information (phone number) to be contacted by the researcher and verbal consent to approach will be documented in the patients’ electronic medical record. The researcher will then discuss the study and answer any questions they might have. If patients indicate that they want to take part, FA will send a patient information sheet describing the project and electronic consent (using the REDCAP eConsent procedure) will be obtained.

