#### Data collection

4.3.3

Before participating in the study, an online baseline assessment questionnaire will be sent. The questionnaire will consist of demographic information, beliefs about medication and medication adherence. Also, included in the demographic information will be questions about their current medication regimen and their most recent HbA1c level. To check the accuracy of self‐reporting, participants answers will be checked with the details of prescribed medication provided in the medical records. The aim of the baseline assessment is to check the validity of self‐reporting and if an online questionnaire is appropriate for this patient group. FA will also interview participants at the end of therapy. The interview will be via phone, last approximately 30 min and will focus on our approach to recruitment, the appropriateness of the measures and the acceptability of the therapy. Interviews will be transcribed and subject to thematic analysis using the approach originally described by Braun and Clark (Braun & Clarke, 2006).

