#### Inclusion criteria

4.7.1

Adults over the age of 18 years.Diagnosed with type 2 diabetes for at least one year.Prescribed any oral or self‐administered injectable medication for the treatment of diabetes (e.g. metformin, insulin).Are non‐adherent to prescribed medication (defined as a Medication Adherence Reporting Scale [MARS] score < 5).

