#### Adherence therapy

4.8.2

A manualized intervention, adherence therapy aims to enhance medication adherence by discussing and carefully challenging patients’ beliefs about medication (e.g. I don't need to take medication if I have no symptoms) and exploring ambivalence about taking medication for diabetes (Gray, 2011). There is also a focus on addressing practical problems (e.g. I forget to take medication) in the adherence therapy approach (Alhalaiqa et al., 2013; Gray et al., 2016). Participants receiving adherence therapy will be sent a SMS about the date/time of the session a day in advance.

In this trial, adherence therapy will be delivered over the phone by FA, a Saudi diabetes educator who trained at the National Guard Hospital. FA will be trained to deliver adherence therapy by RG who initially described the intervention. Training will include a combination of online courses and weekly one‐hour training sessions with RG. In total, FA will attend 12 hr of training. FA will also receive fortnightly supervision from RG and/or DB.

To determine fidelity with adherence therapy, a sample of ten randomly selected sessions will be audio recorded and rated using the Adherence Therapy Scale (ATS) (Gray et al., 2006). Participants will indicate on the consent form if they are willing to have sessions recorded. Not agreeing to have the session audio recorded will not preclude people from participating in the trial.

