#### Recruitment

4.10.3

Recruitment of participants will be undertaken at the outpatient clinic of the National Guard Hospital. Approximately 100 patients with type 2 diabetes are seen each week. We estimate that approximately 50% of patients will be non‐adherent according to our definition (i.e. MARS score ≥ 5). In previous adherence studies, around six patients need to be asked to get one to consent (Chien et al., 2015). This means that we can realistically expect to recruit around four patients per week to the trial. Recruitment can be expected to be completed within 5 weeks. Our recruitment will follow the following process:

Step one (checking eligibility): the treating team working in the diabetes clinic will have access to a list of patients who will be seen in the clinic each day. They will undertake an initial screen (i.e. determine they are over 18 years of age and have a diagnosis of type 2 diabetes).Step two (consent to approach): a member of the treating team will then ask patients if they would be interested in taking part in a research project about adherence to diabetes treatment (consent to approach). If they say yes, they will be given a patient information sheet and ask the patient to complete the MARS. At this time, patients will also be told that only patients who regularly miss their medication will be included in the study. Patients who score below seven on the MARS will be informed they meet inclusion criteria and be asked to provide consent. Adherent patients (i.e. those with a MARS score above eight) will be informed that “because adherence does not seem to be a problem for them, they may not benefit from the intervention and on this occasion cannot be included.” Information about the number of people who receive study information and who consent to be approached will be recorded.Step three (informed consent): from patients that meet study inclusion criteria, we will seek online informed consent. FA will explain study procedures and answer any questions participants may have. Participants will have 48 hr to consider taking part in the study at which point online informed consent will be obtained.

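### Part one recruits any four adults with type 2 diabetes, so about two of the four may fall outside the non-adherent group that the therapy and the trial are for

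*Protocol article*

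**What the plan says.** **Part one.** Section 4.3.1 states: "Four adults with type 2 diabetes from the National Guard Hospital in Riyadh, Saudi Arabia will be recruited". It then gives the route in order: approach by the treating team, agreement to be contacted, a call from the researcher, an information sheet and electronic consent. No adherence requirement appears among these steps. Section 4.1 gives the purpose as "To establish the acceptability of the therapy in the Middle East and to identify any required modifications to the intervention". Adherence is recorded, but only at baseline in patients who have already been selected. Section 4.3.3 says: "The questionnaire will consist of demographic information, beliefs about medication and medication adherence". The closing interview "will focus on our approach to recruitment, the appropriateness of the measures and the acceptability of the therapy". Under section 4.3.4 the results may lead to changes in the trial's methods.

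**Part two.** Section 4.7.1 requires patients to be non-adherent "to prescribed medication (defined as a Medication Adherence Reporting Scale [MARS] score < 5". Section 4.10.3 has patients complete the MARS in clinic, where "patients will also be told that only patients who regularly miss their medication will be included in the study". Those found adherent are turned away on the ground that they may not benefit.

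**The therapy.** Section 4.8.2 describes work on beliefs about medication, on "exploring ambivalence about taking medication for diabetes" and on "addressing practical problems (e.g. I forget to take medication".

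**The concern.** Part one is the only planned step in which the therapy is tried and adapted before the trial opens, and it rests on four people. The protocol regards adherent patients as unlikely to gain from the therapy, yet the Part one route lets them make up some or all of those four.

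A patient who takes medication as prescribed probably has less ambivalence to explore and fewer practical problems to solve. Such a patient's opinion of the sessions is then a weaker guide to how trial patients will receive them. With four interviewees, two from outside the target group are half of the evidence on acceptability.

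The other aims of Part one depend much less on adherence. Willingness to take an active role in managing the illness, the part played by religious and cultural beliefs, and whether an online questionnaire suits these patients can all be explored with adherent patients too.

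**Working it through.** **Inputs**
- Part one sample: 4 (section 4.3.1).
- Share of clinic patients who are non-adherent, p: about 50% (section 4.10.3).
- Patients asked per consent: about 6 (section 4.10.3).
- Clinic attendance: about 100 patients with type 2 diabetes a week (sections 4.6 and 4.10.3).
- Planned recruitment period: 5 weeks (section 4.10.3).
- Visit interval: six-monthly, given as an example (section 2).
- Range of p from 40% to 60%: assumed here. Section 2 also cites a published range of 6.9% to 61.5%.

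**The plan's own figure first.** 100 × 0.5 / 6 = 8.3 consents a week, and 40 / 8.3 = 4.8 weeks, which reproduces the stated 5 weeks. The stated four patients a week does not follow from the same inputs (40 / 4 = 10 weeks). That is a separate matter. It is mentioned only because the 50% and the one in six are reused below.

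**Expected number outside the target group**, 4 × (1 − p), with the binomial chance that three or four of the four are outside:

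| p (non-adherent) | Expected outside | P(3 or 4 outside) |
|---|---|---|
| 0.4 | 2.4 | 0.475 |
| 0.5 | 2.0 | 0.3125 |
| 0.6 | 1.6 | 0.179 |

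At p = 0.5, P(at least one outside) = 1 − 0.5⁴ = 0.94. Over the wider range in section 2 the expected number runs from 4 × 0.931 = 3.7 down to 4 × 0.385 = 1.5.

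**Cost of applying the criterion.** Without it, 4 × 6 = 24 patients are asked. With it, 24 / p: 60, 48 and 40 at p = 0.4, 0.5 and 0.6. This takes willingness to consent as unrelated to adherence.

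**Re-entry into Part two.** The exclusions in section 4.7.2 cover current trial participation and current psychological treatment, so a patient who has finished Part one is not barred. If re-approached, such a patient enters with probability q = p / 6 = 1/12 at p = 0.5, and half of entrants become controls.
- All four re-approached: P(at least one becomes a control) = 1 − (1 − 1/24)⁴ = 0.157 (0.127 to 0.185 for p = 0.4 to 0.6).
- Six-monthly visits with independent timing, and 5 weeks of recruitment: q is multiplied by 5/26, giving 0.032 (0.025 to 0.038).
- If Part one takes only non-adherent patients and all still meet the criterion afterwards (worst case, assumed), q = 1/6. The two figures become 1 − (1 − 1/12)⁴ = 0.294 and 0.063.

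**The case against.** **The point rests on silence in a condensed article.** Section 4.2 and the full protocol were not available to this review, and a criterion could stand there. This is why the point is limited to Part one as described. But section 4.3.1 sets out population and route step by step, and that route differs from the trial's.

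**The aim is cultural, and adherence is measured.** Much of this stands. Section 4.1 is mainly about attitudes to taking an active role, which do not depend on the MARS score, and the baseline questionnaire will show which of the four are non-adherent. That adherent patients bring less ambivalence is an inference; the protocol measures beliefs and adherence with separate instruments. What remains is the acceptability of a therapy aimed at non-adherence.

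**The figure of two is soft.** It assumes that those who volunteer resemble the clinic. It also uses a 50% estimate that section 4.10.3 attaches to a MARS score of 5 or more, the reverse of the direction in section 4.7.1. With four patients the actual number could be anything from none to four.

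**Two stronger readings are tempting but unsupported.**
- A reader might infer that nobody will be able to comment on the screening step. The four do not go through the clinic screen, but they complete an adherence measure and are asked about the measures. Sections 4.11 and 4.12 provide for interviews with trial participants in both arms, including on the acceptability of trial procedures. That feedback comes in time for the full trial.
- A reader might infer that returning Part one patients would contaminate the control arm. Re-entry is possible as written, but the chance is about 3% under the protocol's example of visit frequency, and it would touch only descriptive results and interviews. The researcher who delivers Part one therapy also seeks trial consent, so a returning patient would probably be recognised.

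**Conclusion.** The point holds as a modest improvement to the design. Following section 4.3.1, about two of the four Part one patients are expected to be outside the trial's target group (2.4 to 1.6 for non-adherence of 40% to 60%), with a 31% chance of three or four. This rests on the protocol's 50% estimate, on volunteers resembling the clinic, and on no criterion being stated in text not seen.

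The consequence is less relevant evidence on the acceptability of the therapy, in a step that may change the trial. Part one is not invalid, and its findings on cultural fit and online measures keep most of their value. No outcome or estimate of the feasibility trial is wrong because of this.

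**What to change.** 1. In section 4.3.1, recruit the four from patients who meet the trial's MARS non-adherence criterion, using the screening step and message of section 4.10.3.
2. Correct the cut-off first. Five items scored 1 to 5 (section 4.10) sum to at least 5, so a total below 5 cannot occur. Section 4.10.3 uses 5 or more, below seven and above eight in different places. Without one workable value the criterion would admit nobody.
3. As a minor safeguard, add receipt of adherence therapy in Part one to the exclusions in section 4.7.2. This belongs with the first change, which in the worst case roughly doubles the small chance of re-entry as a control (16% to 29%, or 3% to 6% with six-monthly visits).

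**Cost.** Apart from the cut-off correction, two sentences of protocol and ethics wording. About 48 patients would be asked instead of 24 (60 to 40 over the assumed range), roughly half of one week's attendance. The real loss is that no adherent patient's view would be heard.

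**Alternative.** If a mix of adherent and non-adherent patients is wanted for cultural adaptation, state that choice, report each interviewee's baseline adherence beside the themes, and take feedback on the screening step from the Part two interviews.
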